### Item response theory approaches

Similar to the procedure described above, we will also use IRT approaches.
^
34,
35
^ In IRT, each item is treated as providing information about a latent trait, and items are evaluated by how strongly they discriminate between individuals at different levels of that trait (i.e., higher latent severity increases the probability of endorsing higher response categories). Within an exploratory dataset, we will use non-parametric IRT (Mokken scaling) to assess scalability, dimensionality, and item ordering, and to identify poorly discriminating items. Following recommendations by Meijer and Baneke,
^
36
^ we will evaluate solutions across increasing lower-bound scalability thresholds (c), beginning at c = 0.01 and then stepping by 0.05 (i.e., 0.05, 0.10, 0.15 … up to 0.60), selecting the most interpretable solution. Second, using the confirmatory dataset, we will fit parametric IRT graded response models to estimate item parameters (e.g. discrimination and category thresholds) to identify the best fitting model. Hence, we will compute revised sum scores based on the retained items and generate latent trait (weighted) scores for use in downstream analyses within stage 2.
^
37
^ A detailed description of the analysis principles for the IRT approach is outlined in Byrne’s publications.
^
11,
13
^

### Network analytic approaches

Network analysis is a more recent approach to psychometrics, which differs from traditional theories in that it does not assume that symptoms are caused by a single underlying latent trait. Instead, NA conceptualises symptoms as mutually interacting components, represented as a graph in which nodes are symptoms and edges reflect conditional associations between symptoms.
^
38,
39
^ This perspective has been proposed as a clinically intuitive complement to traditional models of psychopathology. Using best practice approaches, we will estimate empirical network structures separately for baseline (pooled across arms) and outcome data (separated by treatment arm). Network analysis will follow an exploratory graphical workflow, to identify the dimensional structure and detect redundant or weakly-performing items. As recommended by Christensen and Golino,
^
40
^ bootstrap-based stability assessment will be applied and empirical networks will be assessed in relation to the bootstrapped samples. Their work also suggests that replication metrics around the ~0.65–0.75 range mark the point at which variables begin to show reduced stability, providing a practical basis for identifying potentially unstable items.
^
12,
40
^ A key goal is to identify a network structure that is stable and configurally invariant across baseline and outcome (or treatment arms). If invariance cannot be achieved, we will proceed with the network solution with fewest/least consequential instabilities. From the final network solution, we will compute (i) revised sum scores based on the retained items, and (ii) weighted “net scores” derived from network loadings/strength. A detailed description of the analysis principles for the NA approach is outlined in Byrne’s publication.
^
15
^

### Stage 2: Does psychometric modelling matter? Modelling change and calculating effect sizes

In stage 2 we apply the psychometrically-derived outcomes from the stage 1 analysis to evaluate whether psychometric refinement alters estimated antipsychotic treatment effects compared to original total scores.

### Primary analyses: Continuous outcomes

For each instrument (PANSS and BPRS), outcome symptom severity will be modelled as a function of treatment assignment, adjusting for baseline symptom severity and accounting for clustering of participants within trials via random intercepts, as per best practice RCT modelling.
^
41
^ Detached from the psychometric modelling approach (CFA, IRT, NA) in Model 1 the overall effects of antipsychotics versus placebo, using conventional scoring (i.e., original raw scores) will be estimated. Model 2 comprises a set of related models that mirror Model 1, where raw scores are replaced with abbreviated sum scores based on the results of the psychometric analysis from stage 1. In Model 3 psychometrically-informed (weighted) scores, that are derived from the abbreviated models will be established. Model 2 and 3 will be calculated for each psychometric method separately (CFA, IRT, NA). Models 4, 5 and 6 will extend Models 1, 2a-c and 3a-c, by additionally adjusting for participant level covariates:
•Model 1 (conventional scoring): Outcome is the raw total score with treatment group and baseline score as covariates and a random intercept for trial.•Model 2 (abbreviated total scores): Outcome is a simplified total score created after removing redundant items (as per relevant psychometric method) treatment group and corresponding baseline abbreviated score included as a covariates and a random intercept for trial.oModel 2a – factor analysis abbreviated total scoreoModel 2b – IRT abbreviated total scoreoModel 2c – NA abbreviated total score•Model 3 (weighted psychometric scores): Outcome is a psychometrically derived score (e.g., factor score, IRT expected score, or net score) treatment group and corresponding baseline abbreviated score included as a covariates and a random intercept for trial.oModel 3a – factor analytic weighted scoresoModel 3b – IRT weighted scoresoModel 3c – NA weighted scores (net score)•Model 4: Model 1 additionally adjusting for participant-level covariates (e.g. sex, age [where available])•Model 5a-c: Model 2a-c additionally adjusting for the same participant-level covariates•Model 6a-c: Model 3a-c additionally adjusting for the same participant-level covariates

Effect estimates from each model will be transformed into Cohen’s d to facilitate comparison across trials and scoring approaches. The primary effect of interest is the difference between SMDs derived from those derived from conventional scoring and psychometrically-informed outcomes (i.e. Model 1 vs Models 2a-c vs Model 3a-c, and Model 4 vs 5a-c vs Model 6a-c).

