^ To select the optimal model of schizophrenia, the selection process will be guided by established absolute and relative fit indices, information criteria, and internal consistency metrics, including: the Root Mean Square Error of Approximation (RMSEA; < 0.08), Standardised Root Mean Square Residual (SRMR; < 0.08), Comparative Fit Index (CFI; > 0.95), Tucker-Lewis Index (TLI; > 0.95), Akaike Information Criterion (AIC), Bayesian Information Criterion (BIC), and McDonald’s Omega (acceptable >0.70), following established practices.
^
31,
32
^ Similar to the exploratory approach, confirmatory modelling will be performed for baseline and for the primary post-baseline outcomes. For outcome (post-baseline) measurement models, we will estimate the best-fitting model in the pooled sample and then test invariance across key arm categories (placebo vs active; and where feasible across active-arm classes as defined by the standard classification, with McCutcheon’s taxonomy explored in sensitivity analyses). We will retain the best-fitting baseline and post-baseline model(s) to derive factor scores for downstream treatment-effect estimation in Stage 2.
^
33
^

Measurement invariance, i.e. metric invariance (factor loadings are equal) and scalar invariance (intercepts are equal) across sex will be assessed, and differential item functioning examined by mean, standard error, standard deviation, factor loading scores and
*r
^2^
* values. When invariance is violated, psychometrically optimized models will be examined separated by sub-group (e.g., women and men).

The outcomes of these analyses will then be used for further evaluation and discussion (descriptively) on their differences or similarities in all models and datasets. This procedure will include model structure or item functioning (i.e. dropped items, item loadings on factor). Revised sum scores based on the retained items and weighted scores will then be computed from the best performing baseline and combined outcome model for each measure. These will be used for the stage 2 analysis described in the following sections.

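### Models 3a-c and 6a-c adjust a weighted outcome for an unweighted abbreviated baseline score, so the primary SMD comparison is not fully like with like

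*Protocol article*

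**What the plan says.** The section 'Primary analyses: Continuous outcomes' lists the models.

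- **Model 1:** "Outcome is the raw total score with treatment group and baseline score as covariates and a random intercept for trial". Outcome and baseline are on the same scoring.
- **Model 2:** the outcome is the abbreviated total, with "treatment group and corresponding baseline abbreviated score included as a covariates and a random intercept for trial". Again they match.
- **Model 3:** the outcome is a factor score, IRT expected score or net score, but the covariate phrase is that of Model 2: "or net score) treatment group and corresponding baseline abbreviated score included as a covariates".
- **Models 6a-c:** "Model 6a-c: Model 3a-c additionally adjusting for the same participant-level covariates", so they carry the same covariate.

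The same section keeps the two kinds of score apart. For Model 2, "raw scores are replaced with abbreviated sum scores based on the results of the psychometric analysis from stage 1". For Model 3, "psychometrically-informed (weighted) scores, that are derived from the abbreviated models will be established". The Stage 1 sections on factor analysis, IRT and networks also list revised sum scores and weighted scores as separate products.

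The paragraph after the model list makes the difference in SMDs between Model 1, Models 2a-c and Models 3a-c the primary effect of interest, and likewise for Models 4, 5 and 6. It says that estimates will be turned into Cohen's d, without naming the SD used.

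**The concern.** The comparison is meant to show what the scoring does to the estimated treatment effect, so only the scoring should differ between models. As written, Model 3 also changes how well the baseline covariate matches the outcome. A weighted outcome should be predicted best by its own baseline. The unweighted sum would usually predict it less well, which leaves a larger residual SD. Depending on how d is formed, that shows up as a wider interval or as a smaller d for the weighted methods. The Discussion speaks of differences of about 10-15% in effect size and of improved precision, so an avoidable difference between models of even a few percent is worth removing.

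**Working it through.** The article states no figure on this point, so there is none to reproduce. The check has three steps.

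**1. Which score is the covariate?** Setting the three model definitions side by side, the covariate matches the outcome in Models 1 and 2 and not in Model 3. The article's own vocabulary (sum scores abbreviated, Model 3 scores weighted) supports the literal reading.

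**2. Size, by formula.** Let ρ be the correlation of the weighted outcome with its own baseline, and q the correlation of the abbreviated with the weighted score at baseline. Both are assumed. Assume also that the abbreviated baseline predicts the weighted outcome only through the weighted baseline. Then:

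- residual SD with the matched covariate is proportional to √(1 − ρ²);
- residual SD with the abbreviated covariate is proportional to √(1 − (ρq)²);
- a residual-SD d is multiplied by √[(1 − ρ²)/(1 − (ρq)²)];
- the standard error of the treatment coefficient is multiplied by the reciprocal of that factor.

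Example, ρ = 0.5 and q = 0.95: √(0.75/0.774375) = 0.984. A residual-SD d falls by 1.6% and the standard error rises by 1.6%.

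Each cell gives the fall in a residual-SD d, then the rise in the standard error:

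| ρ | q = 0.85 | q = 0.90 | q = 0.95 | q = 0.98 | q = 0.99 |
|---|---|---|---|---|---|
| 0.3 | 1.3% / 1.4% | 0.9% / 0.9% | 0.5% / 0.5% | 0.2% / 0.2% | 0.1% / 0.1% |
| 0.5 | 4.3% / 4.5% | 3.0% / 3.1% | 1.6% / 1.6% | 0.7% / 0.7% | 0.3% / 0.3% |
| 0.7 | 11.1% / 12.5% | 8.0% / 8.7% | 4.4% / 4.6% | 1.8% / 1.9% | 0.9% / 1.0% |

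If d is standardised by the raw outcome SD, its expected value does not change. Under randomisation the treatment coefficient is unbiased whichever baseline covariate is used. Only the standard-error figures then apply.

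**3. Plausible q for a general score.** A one-factor simulation used 150,000 participants per setting, 20 retained items, loadings running from 0.3 or 0.4 up to 0.8-0.9, factor stability 0.6 and a true effect of 0.45 (all assumed). It gave q of 0.984-0.993 and ρ of about 0.55-0.58. With loadings 0.3-0.85:

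- residual-SD d: 0.5245 matched, 0.5215 mismatched, a fall of 0.0030/0.5245 = 0.6%; over all settings 0.4-0.9%;
- raw-SD d: 0.4334 matched, 0.4335 mismatched, no systematic change;
- the matched unweighted sum score over the same items gave a residual-SD d of 0.5113, so mismatched Model 3 (0.5215) was still larger. The same held in every setting.

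**The case against.** The strongest reply is that this is a drafting carry-over with little effect. The wording repeats Model 2, and 'corresponding' may have been meant as the baseline version of the same weighted score. The 'Trial-level analyses' section models change from baseline under both scoring approaches, and change in a weighted score needs a weighted baseline. Both scores come from the same retained items after weak items are removed, so q should be high. The formula also leaves out any positive direct prediction by the abbreviated score, which would shrink the loss.

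Much of this stands on size. It does not remove the point: an analyst who follows the pooled Model 3 as written would enter the sum score, and the trial-level section does not change that model. It does show that a weighted baseline score is needed elsewhere in the plan.

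A reader might infer something stronger: that the primary comparison is tilted against the weighted methods by much of the 10-15% that the Discussion has in mind. The same formula gives falls of 7.5% (ρ = 0.5) and 11.8% (ρ = 0.6) if q = 0.7. The documents do not support that reading. Nothing in them points to q as low as 0.7, and a fall in d at all requires a residual-SD standardiser that the article does not state. A lower q is possible if the weighted score is a domain or bifactor score. Stage 1 does consider correlated-factor and bifactor models, but the model list does not say that Model 3 uses such a score.

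**Conclusion.** The mismatch is real as written and sits in the primary comparison, so Models 3a-c and 6a-c are not compared fully like with like with the other models. The certain consequence is modest: some loss of precision for Model 3 whenever the abbreviated baseline predicts less well than the weighted one. A lower d follows only with a residual-SD standardiser. The fall is then probably about 1% or less for a general score (q about 0.98-0.99, ρ near 0.55-0.58). It is several percent if q is nearer 0.85-0.90 (3.0-4.3% at ρ = 0.5), and reaches 10% only at ρ = 0.7 with q = 0.85. These sizes rest on assumed correlations. This is a specification error that should be fixed before analysis, not a demonstrated bias.

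**What to change.** In Model 3, and so in Models 6a-c, name as covariate the baseline weighted score of the same method: factor score for 3a, IRT score for 3b, net score for 3c. Where possible, score baseline and outcome with the same item parameters or weights. State one standardiser for Cohen's d and use it in all models.

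The cost is one phrase in the model list and a sentence on the standardiser. Stage 1 already plans weighted scores at both time points ("weighted scores will then be computed from the best performing baseline and combined outcome model for each measure"). However, the factor scores are to come from a baseline and an outcome model, and the networks are estimated separately for baseline and outcome. Scores on common parameters are therefore not shown to exist yet and may need one extra scoring step. No new data are needed, and correcting the text now avoids a documented deviation in the primary model later.

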### Trial-level analyses

In addition to pooled IPD analyses, treatment effects will be estimated separately within each trial using both conventional and psychometrically-informed outcome scores. For each trial, change from baseline to outcome will be modelled adjusting for baseline severity, and trial-specific SMDs will be calculated for both scoring approaches. The difference between the psychometrically informed SMD and the conventional SMD will be computed for each trial and treated as the trial-level effect of interest. Potential moderators (e.g. sex) may be explored descriptively or within mixed models where data permits.

### Secondary analyses: Response

Secondary analyses will explore whether psychometric refinement meaningfully alters estimates binary outcomes such as response. Response will be defined using established PANSS or BPRS definition.
^
42–
44
^ Because binary outcomes may be sensitive to how thresholds map onto the underlying scale, these analyses will be treated as exploratory. The change in number of participants between psychometrically informed and original data will then be analysed using multilevel logistic regression models. Models will be fitted with and without adjustment for participant-level covariates.

Analyses will proceed in three steps:
1.Estimate baseline to outcome change in the proportion meeting response criteria within each arm, using both conventional and psychometrically-informed scoring.2.Estimate treatment and comparator differences in response using conventional scoring and psychometrically-informed scoring in separate models.3.Quantify the % difference between these two estimates (psychometrically-informed vs conventional) as the key comparison for secondary outcomes.

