### Outcome measures
*:* PANSS and BPRS

The PANSS
^
1
^ is one of the most widely used clinician-rated outcome measures in schizophrenia research. It comprises 30 items, each rated on a 7-point anchored severity scale (1 = absent to 7 = extreme), which is commonly summarised as three symptom groupings: Positive (7 items), Negative (7 items), and General Psychopathology (16 items), together forming a total score ranging from 30 to 210. Despite its extensive use, heterogeneity in reported factor solutions and item functioning has prompted concerns about the PANSS’ psychometric robustness and its sensitivity to treatment-related change under some conditions.
^
6
^
^,^
^
23
^

The BPRS is another long-established clinician-rated scale frequently used in psychopharmacology research to quantify a broad range of psychiatric symptoms (e.g., thought disturbance, affective symptoms, activation, hostility).
^
2,
24
^ We will utilize the BPRS version comprising 18 items, each rated on a 7-point severity scale (1 = not present to 7 = extremely severe), producing total scores that typically range from 18 to 126. As with PANSS, published work indicates that factor structures and item performance can vary across samples and settings, which is relevant when BPRS totals are used as trial outcomes.
^
7,
8,
25,
26
^

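### The response analysis uses PANSS/BPRS response criteria on shortened and weighted scores without a mapping, so the key secondary comparison can reflect score origin rather than psychometric refinement

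*Protocol article*

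**What the plan says.** All references are to the Protocol article.

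- **Criterion** (Secondary analyses: Response): "Response will be defined using established PANSS or BPRS definition". Three references are cited. No cut-off is given, and the text does not say whether the rule is a percentage change, a point change or an absolute threshold.
- **Step 1:** "Estimate baseline to outcome change in the proportion meeting response criteria within each arm, using both conventional and psychometrically-informed scoring".
- **Step 2:** "Estimate treatment and comparator differences in response using conventional scoring and psychometrically-informed scoring in separate models".
- **Step 3:** "Quantify the % difference between these two estimates (psychometrically-informed vs conventional) as the key comparison for secondary outcomes".
- **Caveat:** "Because binary outcomes may be sensitive to how thresholds map onto the underlying scale, these analyses will be treated as exploratory".
- **Raw metrics** (Outcome measures): for the PANSS, 30 items rated 1 to 7, "together forming a total score ranging from 30 to 210"; for the BPRS, 18 items rated 1 to 7, "producing total scores that typically range from 18 to 126".
- **Psychometric scores** (Primary analyses: Continuous outcomes): Model 2 uses a sum over the retained items. For Model 3, "Outcome is a psychometrically derived score (e.g., factor score, IRT expected score, or net score" is the description. Item response theory approaches also carries latent trait scores into Stage 2.

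No section says how the established criteria are to be carried over to these scores.

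**The concern.** A response rule is tied to the metric on which it was set. A percentage reduction depends on where zero lies, and a cut-off in points depends on the number of items. The PANSS total has a floor of 30 and the BPRS total a floor of 18. A sum of k retained items has a floor of k. A factor or latent trait score is often centred at zero, so about half of participants would have a baseline at or below zero and a percentage reduction would have no fixed meaning.

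If the same criteria are applied under each scoring as the text reads, two scorings with identical information about a patient can classify that patient differently. Step 3 would then report a difference between scorings that comes from threshold placement, and it could be read as a gain or loss from psychometric refinement.

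The wording of step 1 is a smaller matter. It asks for a change over time in a proportion that, under a change-based definition, is zero at baseline.

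**Working it through.** **1. Plan's own figures.** No response rate, cut-off or sample size is stated for this analysis. The scale ranges reproduce: 30 × 1 = 30 to 30 × 7 = 210, and 18 × 1 = 18 to 18 × 7 = 126.

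**2. One patient, every item falling from 4 to 3.**

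| Score | Baseline → outcome | Uncorrected (B − O)/B | Own floor (B − O)/(B − k) | Floor of 30 kept (B − O)/(B − 30) |
|---|---|---|---|---|
| 30 items | 120 → 90 | 30/120 = 25% | 30/90 = 33% | 33% |
| 20 items | 80 → 60 | 20/80 = 25% | 20/60 = 33% | 20/50 = 40% |

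A shortened sum is therefore harmless if its own floor is used and shifted if the full-scale floor is kept. A rule in raw points also shifts: a total of 90 is a mean item score of 3.0 on 30 items but 4.5 on 20.

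**3. Two-arm illustration (all inputs assumed).** 40,000 simulated patients, 30 items rated 1 to 7, baseline total mean 93 and SD 18, larger improvement on active. The zero-centred score is the raw total itself, standardised to baseline, so it contains no psychometric refinement and the correct difference from the raw total is nil. Entries are active minus placebo response, with the odds ratio in brackets.

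| Score and rule | 20% cut | 30% cut | 50% cut |
|---|---|---|---|
| Raw total, floor-corrected | 0.157 (1.88) | 0.145 (1.92) | 0.079 (2.06) |
| 20-item sum, own floor 20 | 0.157 (1.89) | 0.140 (1.86) | 0.077 (1.95) |
| 20-item sum, floor 30 kept | 0.158 (1.91) | 0.152 (1.86) | 0.117 (1.84) |
| Zero-centred score, percentage change | −0.007 (0.97) | 0.002 (1.01) | 0.015 (1.06) |
| Same score returned to raw metric | 0.157 (1.88) | 0.145 (1.92) | 0.079 (2.07) |

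At the 50% cut, keeping the floor of 30 on the 20-item sum raises active-arm response from 0.176 to 0.324. The step 3 figure on the risk-difference scale would be (0.117 − 0.079)/0.079 = +48%, against (0.077 − 0.079)/0.079 = −3% with the sum's own floor. The odds ratio is less sensitive to the floor. On the zero-centred score the treatment effect all but disappears on either scale.

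**4. Dependence on coding (all inputs assumed).** Latent score with baseline mean 0 and SD 1, mean improvement 0.6 SD, outcome SD 1, baseline–outcome correlation 0.5, 20% rule. Half of participants have a baseline at or below 0.

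| Coding of the rule | Improvers called non-responders | Worseners called responders | Response rate |
|---|---|---|---|
| (B − O)/B ≥ 0.2 | 43% | 62% | 58% |
| O ≤ 0.8 × B | 2% | 13% | 74% |
| (B − O)/abs(B) ≥ 0.2 | 7% | 0% | 68% |

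The misclassification figures thus depend on how the rule is programmed. The dependence on origin does not: adding 5 SD to both baseline and outcome leaves every individual change the same, yet brings the response rate to 33% under all three codings.

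**5. Step 1.** For a change-based rule the baseline value is (B − B)/(B − floor) = 0, so the baseline proportion is 0 in each arm under any scoring and step 1 reduces to the proportion responding at outcome.

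**The case against.** The strongest reply has four parts.

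- **The article does not say that raw criteria are applied unaltered.** It cites definitions without stating them, and a fuller analysis plan could contain the mapping. This stands as a limit on what can be claimed. But the article does fix the established criteria, their use under both scorings, and the percentage difference as the key comparison. As written, that comparison is not defined for the scores it compares.
- **The authors already flag threshold mapping and call the analysis exploratory.** True, and it limits the consequences. A label does not make the quantity interpretable, and step 3 still gives it the leading secondary role.
- **Not every weighted score need be zero-centred.** Model 3 names an IRT expected score, which may lie on the item-sum metric, and no centring is stated for net scores. This stands, so the remedy should cover only scores not already on the raw metric.
- **The misclassification figures rest on one coding.** They do, which is why a range is given.

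A reader might go further and infer that response at baseline is zero by definition and that the whole response analysis cannot give a valid comparison. The document does not support either. The zero holds only for a change-based definition; with an absolute severity threshold, step 1 is coherent. Even with a change-based rule, step 1 becomes redundant but steps 2 and 3 are untouched. With the sum's own floor, the raw arm differences are recovered to within 0.005 in the illustration. Returning the zero-centred score to the raw metric restores them too, by construction.

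**Conclusion.** The concern holds as a correctable defect in an exploratory secondary analysis. Established PANSS/BPRS criteria are to be used under scorings with a different floor or no stated origin, and without a mapping the key secondary comparison can be driven by score origin.

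Its size cannot be fixed from the document, because neither the criterion nor the metric of the weighted scores is stated. Under the assumed inputs it runs from negligible (a shortened sum with its own floor) to near-complete loss of the treatment difference (percentage change on a zero-centred score). Between 2% and 43% of improvers and between 0% and 62% of worseners are misclassified, depending on coding. These are illustrations, not predictions for these trials. The primary comparison of SMDs is not affected.

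**What to change.** In Secondary analyses: Response:

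1. State the response criterion: percentage change, point change or absolute threshold, with its cut-off.
2. For a percentage criterion on an abbreviated sum, use (baseline − outcome)/(baseline − k), where k is the number of retained items rated from 1. Use the same floor-corrected rule on the full total (k = 30 for PANSS, 18 for BPRS).
3. For weighted scores not already on the raw metric, first link them to the raw-total metric, by the model-expected total score or equipercentile linking, and then apply the same rule. Otherwise leave weighted scores out of the response analysis.
4. If the criterion is change-based, reword step 1 as the proportion responding at outcome by arm. If it is an absolute threshold, say so, and step 1 can stay.

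The cost is a few sentences and one linking step in the code. No new data are needed, and the primary analysis does not change.

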In this context, psychometric re-modelling using pooled IPD may help clarify which symptom structures replicate reliably, which items contribute meaningfully, and whether abbreviated scales will capture the same responsiveness to treatment or whether weighted scoring yields more accurate estimates of change. Importantly, we do not claim that psychometric refinement necessarily produces clinically meaningful change at the individual level. Rather, the planned analysis evaluates whether relatively modest differences in effect size (e.g., ~10–15% as observed in prior IPD psychometric work) are detectable and may improve the precision, interpretability, or comparability of trial effect estimates. Yet, they can still matter for meta-analytic synthesis, trial power, and the likelihood of detecting true treatment differences under challenging conditions.

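### The key response comparison is a percentage difference between two separately modelled treatment effects, with no effect scale fixed and no paired interval

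*Protocol article*

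**What the plan says.** All of this stands in the Protocol article, section Secondary analyses: Response, unless another section is named.

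- Model: "The change in number of participants between psychometrically informed and original data will then be analysed using multilevel logistic regression models".
- Step 1: "Estimate baseline to outcome change in the proportion meeting response criteria within each arm, using both conventional and psychometrically-informed scoring".
- Step 2: "Estimate treatment and comparator differences in response using conventional scoring and psychometrically-informed scoring in separate models".
- Step 3: "Quantify the % difference between these two estimates (psychometrically-informed vs conventional) as the key comparison for secondary outcomes".
- Status: "Because binary outcomes may be sensitive to how thresholds map onto the underlying scale, these analyses will be treated as exploratory".

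No sentence in the section names the effect measure for the two estimates compared in step 3. The primary analysis does name one (section Primary analyses: Continuous outcomes): "Effect estimates from each model will be transformed into Cohen’s d to facilitate comparison across trials and scoring approaches". The quantity of interest there is a plain difference between standardised mean differences.

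**The concern.** A percentage difference between two effect estimates is defined only once their scale is defined. The section gives cues in two directions. Multilevel logistic regression yields log odds ratios or odds ratios, whereas the proportions of step 1 and the differences of step 2 suggest a risk difference.

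The choice matters because rescoring can change who counts as a responder in both arms, a sensitivity the section itself recognises. When the comparator rate moves, the risk difference, risk ratio and odds ratio need not move together, even if the drug separates the arms exactly as before.

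There is a second weakness that holds on any scale. Both scorings are applied to the same participants, so the two estimates are strongly correlated. Separate models supply two standard errors but not the covariance between the estimates, so they give no valid interval for the comparison.

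At stake is whether an exploratory statement that refined scoring raises or lowers the drug effect on response can be interpreted.

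**Working it through.** **Inputs.** The article gives no response rates, effect size or precision for this analysis, so there is no stated figure to reproduce. Everything below is assumed: normally distributed scores, a drug effect d that is the same under both scorings, and a responder threshold that moves. The only benchmark in the article is in the Discussion, "relatively modest differences in effect size (e.g., ~10–15% as observed in prior IPD psychometric work) are detectable", and it concerns effect size, not response.

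**Formulas.** Active rate: p1 = 1 - Phi(z(1 - p0) - d), with p0 the placebo rate. RD = p1 - p0; RR = p1/p0; OR = [p1/(1 - p1)]/[p0/(1 - p0)]. Percentage difference = 100 x (refined/conventional - 1).

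**Step 1: modest shift, d = 0.45 throughout.**
- Conventional, p0 = 0.25: p1 = 0.411, OR = 2.095, log OR = 0.740, RR = 1.645, RD = 0.161.
- Refined, p0 = 0.20: p1 = 0.348, OR = 2.132, log OR = 0.757, RR = 1.738, RD = 0.148.
- Percentage difference: OR +1.8%, log OR +2.4%, RR +5.7%, RD -8.4%.

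**Step 2: range of shifts, d unchanged within each row.**

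| d | Placebo rate | OR | log OR | RR | RD |
|---|---|---|---|---|---|
| 0.45 | 25% to 30% | -1.1% | -1.5% | -4.7% | +5.7% |
| 0.45 | 25% to 40% | -2.0% | -2.7% | -12.2% | +10.4% |
| 0.45 | 25% to 12% | +7.1% | +9.2% | +18.7% | -29.1% |
| 0.40 | 30% to 20% | +2.7% | +4.1% | +9.7% | -14.0% |

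The third row is an extreme case, because it roughly halves placebo response.

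**Step 3: a real gain.** Let d rise 10%, from 0.40 to 0.44. With the placebo rate fixed at 30%: OR +6.6%, log OR +9.9%, RD +10.5%. With the placebo rate moving from 30% to 20%: OR +9.6%, log OR +14.2%, RR +14.5%, RD -4.3%.

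**Step 4: the cause.** With the placebo rate fixed, RD, RR and OR all rise with the active rate, so their signs must agree. For 30% placebo and 45% to 48% active: RD +20.0%, RR +6.7%, OR +12.8%. Disagreement in sign therefore needs a moving comparator rate. OR and log OR agree in sign as long as both odds ratios exceed 1.

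**Step 5: the interval.** Assume 500 participants per arm, d = 0.45, a placebo rate of 25% under both scorings, and a correlation of 0.95 between scorings.
- Variance of one arm's log odds, times n, is 1/[p(1 - p)]: 5.333 for placebo, 4.130 for active.
- Covariance between scorings, times n, is (p11 - p^2)/[p(1 - p)]^2, with p11 the probability of response under both scorings (0.2098 placebo, 0.3619 active): 4.190 and 3.290.
- Treated as independent: SE = sqrt{2 x (5.333 + 4.130)/500} = 0.195.
- Paired: SE = sqrt{[2 x (5.333 + 4.130) - 2 x (4.190 + 3.290)]/500} = 0.089.

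Ignoring the pairing roughly doubles the standard error of the difference in log odds ratios. The ratio does not depend on the number per arm.

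**The case against.** The strongest defence is that the section already points to a scale. It prescribes logistic regression, whose output is a log odds ratio, and names neither the risk ratio nor the risk difference as an effect measure. On that reading the sign is stable, and a 5-point shift in placebo response produces an artefact of about 1% to 2.5%, well below the 10–15% in the Discussion. This largely stands. What it does not settle is odds ratio against log odds ratio, which differ in size, or the competing cues in steps 1 and 2.

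Second, the section gives threshold sensitivity as its reason for calling the analysis exploratory, and step 1 will make shifts in response rates visible. That stands and lowers the weight of the point. An unshown analysis plan could also name the scale and the interval method. But the percentage, the separate models and the status of key comparison are fixed in this text.

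Three stronger readings are tempting and should be resisted.
- A reader might infer that naming a scale cannot help and that only a new form of contrast removes the artefact. It does not: a ratio of odds ratios minus 1 is the percentage difference in odds ratios. For 25% to 12%, the ratio of 1.071 is the same +7.1%, while the risk difference falls by 4.7 points (16.1 to 11.4).
- A reader might take the roughly -7% change in the odds ratio of non-response, in the same case, as a reversed conclusion. It is not: a smaller odds ratio of non-response is also a stronger drug effect.
- A reader might infer from the sentence on the number of participants that a net count is the quantity analysed. Steps 1 to 3 concern response by arm under each scoring, so this is loose wording.

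**Conclusion.** The point holds with low severity. The key response comparison has no fixed effect scale. Its size depends on the scale, and its sign can differ between the risk difference and the odds or risk ratio if rescoring moves the comparator response rate. For shifts of 5 points from 25%, the assumed cases give 1% to 2.5% in absolute size on the odds scales and about 5% to 8% on the others, with no change in drug effect. Sign disagreement is possible, not certain: the article allows for threshold effects but reports no shift in response rates.

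The more robust defect is the missing pairing, which applies even if odds ratios are intended. With a correlation of 0.95 between scorings, treating the estimates as independent roughly doubles the standard error. That correlation, the response rates and d are all assumptions. The analysis is exploratory, and the primary comparison of standardised mean differences does not depend on it.

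**What to change.** - Replace steps 2 and 3 by one stacked logistic model for each refined scoring, with two response indicators per participant (conventional and refined). Include treatment, scoring and treatment-by-scoring terms, and trial effects that let the scoring effect vary by trial. Obtain uncertainty by clustering on participant or by bootstrapping participants.
- Make the treatment-by-scoring term, reported as a ratio of odds ratios with its paired interval, the single key comparison in place of the percentage difference.
- Report arm-specific response rates under each scoring and the change in risk difference in percentage points as descriptive context. State that neither contrast is free of threshold shifts.
- Reword the sentence on the number of participants so that the logistic outcome is each participant's responder status. A cross-classification of responder status under the two scorings, by arm, is an optional extra. With a correlation of 0.95 and equal response rates, about 8% (25% rate) to 9% (33% rate) of participants would change status with no net change.

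The cost is plan wording and modest programming, with no new data. A ratio of odds ratios is less intuitive to lay readers than a percentage, which the percentage-point difference offsets.
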